• Patients below the age of 18 years • Pregnant, immunocompromised or undergoing chemotherapy, on steroids or immunosuppressive drugs in the last year or with liver cirrhosis • Co-infection with a non-dengue pathogen • Cases with a lab-confirmed dengue infection within the past three months

The study is designed to investigate the progression of dengue infection in patients, from without warning signs, to with warning signs to severe dengue, which varies between cases. If a patient recruited in the category “DwoWS” develops symptoms correlating with severity and receives intensive care, they will then be re-categorized into the second “DWS” or third “SD” group. Keeping in mind the complexity of dengue presentation, subcategorization of the patients will be performed as necessary to establish the degree of severity depending on the timepoint of recruitment and the points of sample collection. The highest (peak) severity category reached during the acute illness constitutes the participant’s definitive severity classification and serves as the primary outcome label for all biomarker analyses. For incorporation into the biomarker discovery and validation analyses, the earliest sample for each participant collected before or at the point of clinical deterioration is used as the predictor, and the definitive peak severity category is used as the outcome.

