### Study procedures

A single blood sample is collected from the non-hospitalized patients, while two blood samples per participant are collected from the hospitalized patients. The first one is taken within the first two days of hospitalization, and the second at discharge. A questionnaire is administered at the time of blood collection (Table 2). Total participation time is less than 15 min. For Guatemala, whole blood is collected in Tempus™ tube for transcriptomics and in Cytodelics medium for flow cytometry, while plasma from EDTA blood and serum are collected for proteomics, metabolomics and glycomics. For India, whole blood (3 ml) is collected in Tempus™ tubes for transcriptomics and 7–8 ml in BD Vacutainer CPT™ Cell Preparation Tubes for plasma separation and PBMC isolation.

**Table 2 Tab2:** Routine clinical investigations performed in dengue cases in all the cohorts

Parameters	Unit of Measurement
Age	In years
Sex	Male/Female

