**Disease symptoms at the time of sampling**	
Duration of symptoms onset at sample collection	In days
Duration of hospitalization at sample collection	In days
Fever	Yes/No
Body pain	Yes/No
Joint pain (arthralgia)	Yes/No
Rash	Yes/No
Nausea/vomiting	Yes/No
Night sweats	Yes/No
Retro-orbital pain	Yes/No
Abdominal pain	Yes/No
Headache	Yes/No
Chills/ rigor	Yes/No
Burning micturition	Yes/No
Dizziness	Yes/No

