### Statistical analysis

Differential expression analyses will be conducted separately for transcriptomic, proteomic, metabolomic and glycomic datasets with correction for multiple hypothesis testing. Integrated pathway and network analyses will be used to identify dysregulated biological processes associated with disease severity. Validation analyses will be performed using independent cohorts. As there are no high-dimensional studies with such large proteomics (> 1000 proteins) and metabolomics (> 1000 metabolites) in dengue, we have used the RNASeqSampleSize [16] to calculate the sample size for the RNA sequencing based on prior data for other viruses. Prior data indicates that the minimum average read counts among the prognostic genes in the control group is 5, the maximum dispersion is 0.5 and the ratio of the geometric mean of normalization factors is 1. If the total number of genes for testing is 20,000, the top 100 genes are prognostic and the desired minimum fold change is 2, then we will need to study 67 subjects in each group to reject the null hypothesis that the population means of the two groups are equal with probability (power) 0.8 using the Fisher’s exact test. The FDR associated with this test of this null hypothesis is 0.01. Assuming the 30% loss of samples due to the quality, we will keep 100 samples in each group for the discovery cohorts and 150 samples in each group for the validation cohorts. Beyond the RNA-seq–based calculation, the retained cohort sizes (100 per group in the discovery cohort and 150 per group in the validation cohort, after an assumed 30% attrition for sample quality) are adequate for the proteomic, metabolomic, glycomic and machine-learning analyses. The RNASeqSampleSize estimate is conservative, as RNA-seq interrogates by far the largest feature space (~ 20,000 genes) and carries greater technical dispersion than targeted proteomic and metabolomic platforms. The Olink^®^ Reveal assay measures 1,034 proteins with high reproducibility, and the LC-MS/MS metabolomic platform quantifies ~ 1,200 features, an order of magnitude fewer tests than RNA-seq. The N-glycomic analysis similarly involves a considerably smaller number of quantified glycan features. Because these targeted platforms interrogate substantially fewer analytes with lower technical variability, the sample size derived for RNA-seq represents a conservative bound expected to provide comparable or greater statistical resolution for the proteomic, metabolomic and glycomic comparisons. For the machine-learning analyses, robustness is ensured primarily through dimensionality reduction and feature selection prior to model training, together with the prospective discovery-and-validation design and external cross-site validation.

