Several limitations warrant consideration. As an observational study, COMBAT cannot establish causal relationships between identified molecular signatures and clinical outcomes. Differences in timing of sample collection relative to symptom onset may influence observed molecular profiles. In addition, variability in transmission patterns and diagnostic capacity across sites may affect recruitment rates and cohort composition. Although laboratory-based inclusion criteria strengthen internal validity, they may reduce the ability to capture the full clinical spectrum of dengue-like illness during low-transmission periods. Achieving an appropriate balance between methodological rigor and epidemiological representativeness remains a central challenge in cohort-based infectious disease research. Finally, although we aim to develop a unified biomarker panel applicable across both settings, differences in host genetic background, environmental exposures, and other population-specific factors may limit the identification of a fully overlapping biomarker signature. In such cases, we will develop and validate region-specific biomarker panels while also identifying conserved biological pathways that may support broader cross-population applicability.

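### Sampling is not anchored to symptom onset and no handling of illness day is stated for the severity comparisons, so time-course markers may be reported as severity markers

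*Protocol article*

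**What the plan says.** **Timing of samples.** Under Study procedures, for outpatients, "A single blood sample is collected from the non-hospitalized patients", with no window in days of illness. For inpatients, "The first one is taken within the first two days of hospitalization, and the second at discharge". The tube types differ between Guatemala and India, but the timing rule is the same.

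**Sample used.** Under Study cohorts, "the earliest sample for each participant collected before or at the point of clinical deterioration is used as the predictor", and the outcome label is the peak severity reached. The same section allows patients to be subcategorized as needed, "depending on the timepoint of recruitment and the points of sample collection", without saying how.

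**Disease phases.** The Background puts the febrile phase at days 1–3 and the critical phase, when plasma leakage may lead to shock, at days 4–6. Table 1 defines severe dengue (SD) partly by severe plasma leakage.

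**Analysis.** The Statistical analysis section says "Differential expression analyses will be conducted separately for transcriptomic, proteomic, metabolomic and glycomic datasets with correction for multiple hypothesis testing". The section on multi-omics studies and biomarker identification adds Random Forest feature selection and Bayesian network modelling. Neither gives illness day a role.

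**What is recorded and acknowledged.** Table 2 collects "Duration of symptoms onset at sample collection" in days, together with age and sex. The Discussion describes host profiles in acute viral infection as changing quickly with time from onset and calls for temporally harmonized cohorts. Its limitations paragraph says "Differences in timing of sample collection relative to symptom onset may influence observed molecular profiles" and offers no remedy.

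**The concern.** The first primary endpoint is a set of signatures that differ across severity categories. If patients with SD are on average sampled later in the illness than patients with dengue without warning signs (DwoWS), a feature that simply rises or falls with time will differ between the groups even if it has nothing to do with severity.

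The plan's timing rules make such an imbalance likely. A patient who is already severe at recruitment because of plasma leakage is, by the article's own phases, likely to be in days 4–6. A sample taken at deterioration in such a patient is compared with a presentation sample from an outpatient who may still be febrile.

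The plan relies on the independent cohort as its main safeguard. That gives little protection against a bias that comes from the sampling rule, because India follows the same rule. A time-course marker could pass discovery, pass validation and take one of the 5–10 places on the Flex panel.

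**Working it through.** **1. The plan's own figure.** Inputs from the Statistical analysis section: 20,000 genes, 100 prognostic, FDR 0.01, power 0.8, mean count 5, dispersion 0.5, fold change 2.

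- Implied per-test alpha = (0.8 × 100 × 0.01) / [(20,000 − 100) × 0.99] = 0.8 / 19,701 = 4.06e-5; two-sided critical value z = 4.104.
- Wald approximation on the log fold change: variance term = (1/5 + 0.5) + (1/10 + 0.5) = 1.3. n = (4.104 + 0.842)² × 1.3 / (ln 2)² = 66.2, so 67 per group.
- Exact two-group negative binomial test at n = 67: power 0.804.

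The stated 67 reproduces as a plain two-group comparison, with no allowance for a covariate. The planned 100 per group leaves 100 × 0.7 = 70 after the assumed 30% loss.

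**2. Chance that a pure time-course marker is called.** The documents give no distribution of illness day by group and no rate of change for any marker. Both are assumptions here: slope 0.3 or 0.4 within-group SD per day, group difference 0.5 to 2 days. The induced standardized difference is d = slope × difference in days, and the chance of a call is Φ(d × √(70/2) − 4.104).

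| Day difference | Slope 0.3 | Slope 0.4 |
|---|---|---|
| 0.5 | d = 0.15: 0.0006 | d = 0.20: 0.002 |
| 1 | d = 0.30: Φ(1.775 − 4.104) = 0.01 | d = 0.40: Φ(2.366 − 4.104) = 0.04 |
| 2 | d = 0.60: Φ(3.550 − 4.104) = 0.29 | d = 0.80: Φ(4.733 − 4.104) = 0.74 |

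If the slope is instead expressed in residual SD and illness day itself has an SD of 1 day, the total SD is √(1 + slope²), and the 2-day figures become 0.24 and 0.61. On that scale, a wider slope range of 0.25 to 0.5 gives 0.004 to 0.07 at 1 day and 0.11 to 0.88 at 2 days.

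**3. Whether validation would catch it.** Assume that the same imbalance recurs in India, that 150 × 0.7 = 105 per group are retained, and that 10 candidates are tested with Bonferroni correction (alpha 0.005, z = 2.807). The chance that the marker passes is Φ(d × √52.5 − 2.807). At d = 0.6 this is Φ(4.347 − 2.807) = 0.94; at d = 0.3 it is Φ(2.174 − 2.807) = 0.26.

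**4. Cost of adjusting.** If group means differ by g SDs of illness day, the share of illness-day variance explained by group is R² = (g²/4) / (1 + g²/4), and the required size grows by 1/(1 − R²) = 1 + g²/4.

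- g = 0.5: 67 × 1.0625 ≈ 71
- g = 1: 67 × 1.25 ≈ 84
- g = 2: 67 × 2 = 134

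These compare with 70 retained, before any gain from residual variance that illness day removes.

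**The case against.** The text is a condensed article, and a covariate list commonly sits in a full protocol or SAP that is not shown. The article does not say that the analysis is unadjusted, and a two-group sample-size calculation does not show that it is. A reader might infer that the groups will be compared without adjustment; the documents do not support that, because silence is not a decision.

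Nor does any section report illness day by severity group. Outpatients have no stated window, so they cannot be shown to be sampled earlier, and the two-day limit for inpatients is only an upper bound. Taking the earliest eligible sample and labelling it by peak severity also works against the bias: a patient who enters as DwoWS and progresses contributes an early sample to the SD group. The machine-learning models take clinical and demographic data, which could include days since onset. Subcategorization by time point is allowed, and the Discussion describes the biomarkers as time-aware.

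These points limit the claim but do not remove it. The issue goes beyond an unnamed covariate. The article itself fixes a sampling rule that can link illness day to severity, says that timing matters, and then treats it only as a limitation. The subcategorization is unspecified. The machine-learning inputs do not name illness day and do not cover the differential expression behind the first primary endpoint.

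The argument for age and sex is weaker. Matching is stated only for healthy controls, but no imbalance among the dengue groups is shown.

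**Conclusion.** The point holds in this form: illness day is likely to differ between severity groups under the sampling rules, no handling of it is stated in the severity comparisons, and time-course markers may therefore be reported as severity markers and may replicate in India.

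The group difference is an inference from the disease phases and the sampling rules. The size cannot be fixed from the documents. With the assumed slopes of 0.3 to 0.4 SD per day, the risk is negligible at half a day, about 0.01 to 0.04 per marker at 1 day, and 0.29 to 0.74 at 2 days.

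A reader might infer from the 2-day figures that false severity markers will be reported. That is too strong, because it depends on a day difference and marker slopes that nobody has yet reported. The change is still worth making: a primary endpoint is exposed, the variable is already collected, and enrolment stood at 170 of 400 (4 groups × 100) in Guatemala in June 2026, with India only starting in July 2026.

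**What to change.** For contrasts among the three dengue groups:

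- Include days since symptom onset, for example as a smooth term, in the differential models and in feature selection, with age and sex as secondary covariates.
- Name days since onset as an input to the prediction models.
- Report the distribution of illness day by severity group and cohort.
- Add a sensitivity analysis restricted to the range of illness days where the groups overlap.

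The adjustment cannot extend to contrasts with healthy controls, who have no onset day.

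No new data are needed, but the change has a price. Precision falls as the day imbalance grows: 67 per group becomes about 84 if group means differ by one SD of illness day, against 70 retained, before any gain from reduced residual variance. The sensitivity analysis will have smaller numbers. Where groups hardly overlap in illness day, adjustment rests on extrapolation, so the distribution is best examined while recruitment continues.

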### Study status

Prospective recruitment and sampling commenced in January 2025 and is ongoing at all participating sites. As of June 2026, 170 participants had been enrolled across the four study groups (DwoWS, DWS, SD and healthy controls) in the Guatemala (discovery) cohort; recruitment of the India (validation) cohort is initiated in July 2026 following the funding body approval. Recruitment is anticipated to be completed by November 2027, or earlier should the target sample size (100 participants per group in the discovery cohort and 150 per group in the validation cohort) be reached sooner. Because dengue transmission is cyclical and epidemic-dependent, recruitment timelines are contingent on local outbreak dynamics; should enrolment at any site fall behind target, pre-specified additional cohorts and biobanked samples will be accessed as a mitigation strategy, subject to approval by the COMBAT General Assembly.

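### The sample-size text calls the enrolment numbers (100 and 150 per group) retained after 30% attrition; 70 and 105 remain, and adequacy for the platforms other than RNA-seq is asserted but not established

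*Protocol article*

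**What the plan says.** All the sizing is in the Statistical analysis section of the protocol article. The inputs are "the minimum average read counts among the prognostic genes in the control group is 5, the maximum dispersion is 0.5", with a normalization ratio of 1. Further, "If the total number of genes for testing is 20,000, the top 100 genes are prognostic and the desired minimum fold change is 2". The stated result is 67 subjects per group "with probability (power) 0.8 using the Fisher’s exact test" at an FDR of 0.01.

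Two sentences then give the 30% loss opposite roles:

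- First: "Assuming the 30% loss of samples due to the quality, we will keep 100 samples in each group for the discovery cohorts" and 150 for validation. Here 100 and 150 are the numbers before loss.
- Next: "the retained cohort sizes (100 per group in the discovery cohort and 150 per group in the validation cohort, after an assumed 30% attrition". Here 100 and 150 are the numbers after loss. This sentence declares those sizes adequate for the proteomic, metabolomic, glycomic and machine-learning analyses.

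The Study status section gives a "target sample size (100 participants per group in the discovery cohort and 150 per group in the validation cohort") as the point at which recruitment can end. Study cohorts gives 100 and 150 per category as the numbers to be collected, and Recruitment of controls gives 100 and 150 healthy participants as enrolled.

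For the other omics platforms the section argues that "the sample size derived for RNA-seq represents a conservative bound expected to provide comparable or greater statistical resolution". Its grounds are that they measure fewer analytes and have lower technical variability.

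**The concern.** If 100 and 150 are enrolled, they cannot also be what is left after losing 30%. The retained figure is not incidental: it is the subject of the sentence that declares four further types of analysis adequately sized. The conservative-bound argument is a second, separate support for the omics part of that claim, and it needs checking in its own right because it is attached to the RNA-seq calculation and not to 100 or 150.

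The proteomic layer matters most. According to the section on the Flex panel, it feeds the 5–10 marker panel intended for clinical deployment, and a validated multi-omics-derived panel is a primary endpoint. A reader told that every platform is adequately sized may give a negative proteomic finding more weight than the design can support.

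**Working it through.** **1. Reproduce the plan's figure.** Inputs from Statistical analysis: 20,000 genes, 100 prognostic, fold change 2, control mean count 5, dispersion 0.5, power 0.8, FDR 0.01.

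- Per-gene alpha = power × m1 × FDR / [(m − m1)(1 − FDR)] = 0.8 × 100 × 0.01 / (19,900 × 0.99) = 4.06e-5; two-sided z = 4.104.
- Log-scale variance, both groups: (1/5 + 0.5) + (1/10 + 0.5) = 1.3.
- n = (4.104 + 0.842)² × 1.3 / (ln 2)² = 66.2, so 67.
- An exact conditional negative-binomial test gives power 0.793 at 66 and 0.804 at 67.

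The plan's 67 is correct.

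**2. Which side of the loss is 100 on?** 67 / 0.7 = 95.7, so 96, which the plan rounds up to 100. It is therefore the inflated enrolment number, as the other three sections confirm.

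| Cohort | Enrolled | Remaining after 30% loss | Enrolment needed to retain the stated number |
|---|---|---|---|
| Discovery | 100 | 100 × 0.7 = 70 | 100 / 0.7 = 143 |
| Validation | 150 | 150 × 0.7 = 105 | 150 / 0.7 = 215 |

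Overstatement: 100/70 = 150/105 = 1.43, or 43%.

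**3. Effect on RNA-seq.** The exact test gives power 0.833 at 70, 0.976 at 100 and 0.983 at 105. The target of 0.8 is met in both cohorts after loss.

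**4. Do fewer analytes make the RNA-seq size conservative?** Apply the same alpha formula at the 0.5% prognostic share that the plan uses for genes (an assumption for the other platforms):

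| Platform | Prognostic / tested | Per-test alpha | Detectable difference at n=70, 80% power |
|---|---|---|---|
| RNA-seq | 100 / 20,000 | 4.06e-5 | 0.84 SD |
| Proteins | 5 / 1,034 | 3.93e-5 | 0.84 SD |
| Metabolites | 6 / 1,200 | 4.06e-5 | 0.84 SD |

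Detectable difference = (z + 0.842) × √(2/n). At an equal share, a smaller number of features does not relax the threshold. A higher share does: for proteins at n=70 the figure is 0.81 SD at 10 of 1,034, 0.74 SD at 50 of 1,034, and about 0.70 SD at a 10% share.

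**5. Does lower technical variability make it conservative?** The gene assumption corresponds to a standardized difference of ln 2 / √0.65 = 0.86 SD, using the average per-group variance 1.3/2. To carry the size across, the other platforms need standardized effects about that large. Technical precision removes one component of variance. It bounds neither the variance between subjects nor the size of the biological difference, and the document gives no figure for either.

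**6. How much the label could matter.** For proteins at a 0.5% share and FDR 1%, a 0.7 SD difference (assumed for illustration) has power 0.51 at 70 and 0.80 at 100.

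**The case against.** The strongest reply is that the slip leaves the only formal calculation intact, since 70 and 105 both exceed 67. That stands. The word retained may also be loose wording for kept with an allowance for loss. As printed, though, the sentence says after attrition, and an adequacy claim is built on it.

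The conservative-bound argument also has some basis. The gene inputs are described as worst case (minimum count, maximum dispersion). If the counting noise is removed (0.3 of the 1.3 variance), the same fold change and dispersion need (4.104 + 0.842)² × 1.0 / (ln 2)² = 50.9, so 51 per group, and power at 70 rises to about 0.95. This shows the bound could hold. It does not show that it does, because it still assumes twofold effects and the same between-subject dispersion for proteins, metabolites and glycans.

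A reader might go further and infer that proteomics is underpowered, for example from power of 0.12 for a 0.5 SD protein difference at 70 per group. The documents do not support this. The 0.5 SD, the 0.5% share and the 1% FDR for proteins are the reader's assumptions; for the other platforms the plan states only that multiple testing will be corrected. Moreover, candidates are first selected by Random Forest and Bayesian networks, so a protein need not pass a 1% FDR test to reach the panel.

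Nor should 0.68 SD at 105 per group be read as the resolution of panel validation. It carries the multiplicity of 1,034 proteins into a test of 5–10 markers. With Bonferroni for 10 markers at 5% (an assumption), the figure is (2.807 + 0.842) × √(2/105) = 0.50 SD.

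Finally, an article may leave platform-specific detectable differences and AUROC precision to the full protocol or SAP. Their absence is not the point; the affirmative claim of adequacy is. On machine learning, the section does say that robustness comes primarily from feature selection and external validation. That is a fair statement of approach, but it does not show that the size is adequate.

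**Conclusion.** The enrolled and retained numbers are confused. Under the plan's own 30% loss, 70 and 105 per group are analysable, and the stated retained sizes are 43% too high. This rests only on the document's figures. RNA-seq sizing is correct and survives the loss, with power of about 0.83 at 70.

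The conservative-bound argument does not follow. Its first ground fails at an equal prognostic share, and its second says nothing about effect size or between-subject variance. Adequacy for proteomics, metabolomics, glycomics and machine learning is therefore not established, which is different from being refuted: larger standardized effects or a higher prognostic share could make the sizes sufficient. The correction is worth making, but it does not call the design into question and is not critical.

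**What to change.** - State 100 and 150 per group as enrolled, and 70 and 105 per group as the expected analysable numbers after 30% loss.
- Delete or qualify the conservative-bound statement, and the statement that the sizes are adequate for the other platforms and for machine learning.
- If a discovery figure is offered, print its assumptions with it. For proteins at 70 per group, FDR 1% and 80% power, the detectable difference is about 0.84 SD at a 0.5% prognostic share and about 0.70 SD at 10%.
- Do not apply discovery multiplicity to the validation of the 5–10 marker panel.

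The change is to text only and needs no extra participants. Its cost is that the stated sizes, and what is claimed from them, become less favourable.

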#### Multi-omics studies and biomarker identification

We will perform RNA sequencing (RNA-seq) of the blood cells [10], proteomics by Olink^®^ Reveal, and metabolomics using liquid chromatography-mass spectrometry (LC-MS/MS) in the samples collected from Guatemala [11, 12]. Due to different numbers of analytes, i.e., genes from RNA-seq (n = ~ 20000), protein (n = ~ 1034) and metabolites (n = ~ 1200), we will first identify biomarkers associated with disease severity in each omics dataset using Random Forest for feature selection, and Bayesian belief network (BBN) based structural causal modelling to infer putative causal relationships [12]. To further refine the biomarkers, we will perform integrative analysis using the Consensus Association (CA) analysis and gene/protein/metabolite cooperation networks by integrating the transcriptomics, proteomics and metabolomics analysis to identify a robust mechanism-informed protein biomarker panel for clinical translation [9]. Additionally, a high-throughput analysis of total plasma, IgG, and/or IgM N-glycome [13, 14] from the available patient cohorts will be performed to evaluate glycosylation as a biomarker of disease severity. For Indian samples we will perform RNA-seq of the blood cells and proteomics by Olink^®^ Reveal.

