#### Artificial intelligence (AI) models for DENV severity

The assessment of DENV severity using traditional methods has proven difficult due to many contributing factors, such as variation in symptoms, dynamic nature of dengue infection, and lack of specific biomarkers, amongst others [8]. Multiple machine-learning and deep-learning models, including logistic regression, random forests, XGBoost, support vector machines, multilayer perceptrons, and multimodal neural-network architectures, will be trained and systematically compared for DENV severity prediction. The models will integrate available clinical, laboratory, demographic, virological, and multi-omics data, using feature-selection and dimensionality-reduction approaches. Model interpretability will be assessed using explainable AI approaches, including SHapley Additive exPlanations (SHAP) and Local Interpretable Model-agnostic Explanations (LIME), to identify the variables and molecular features driving individual- and cohort-level predictions. Temporal and geographical robustness will be evaluated using time-split validation, external validation across sites, and leave-one-site-out cross-validation. Model performance will be assessed using AUROC, AUPRC, sensitivity, specificity, F1-score, calibration, and decision-curve analysis to identify clinically robust and generalizable models for DENV severity prediction.

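### The cohort is called adequate for machine learning with no calculation that sizes a prediction model, and the sizes called retained after 30% loss are enrolment numbers

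*Protocol article*

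**What the plan says.** The Statistical analysis section of the protocol article contains one sample-size calculation, for RNA-seq. Its inputs are that "the minimum average read counts among the prognostic genes in the control group is 5, the maximum dispersion is 0.5", that "the ratio of the geometric mean of normalization factors is 1", and "If the total number of genes for testing is 20,000, the top 100 genes are prognostic and the desired minimum fold change is 2". The result is 67 per group "with probability (power) 0.8" at a false discovery rate of 0.01. A 30% loss for sample quality is then assumed, giving 100 per group in discovery; validation is set at 150.

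The section next describes 100 and 150 as the sizes retained after that loss and says that they "are adequate for the proteomic, metabolomic, glycomic and machine-learning analyses". For the other omics layers it argues from fewer analytes and lower technical variability. For machine learning it relies on dimension reduction, feature selection before training, the discovery-and-validation design and cross-site validation. It gives no figure.

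Under Study status, 100 and 150 participants per group are the recruitment target.

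Three other sections bear on the point. In Multi-omics studies and biomarker identification, features are first selected within each omics dataset, and layers are then combined "by integrating the transcriptomics, proteomics and metabolomics analysis to identify a robust mechanism-informed protein biomarker panel". In the section on AI models, "multilayer perceptrons, and multimodal neural-network architectures, will be trained and systematically compared for DENV severity prediction", alongside simpler models. In Study procedures, Guatemalan RNA comes from a Tempus tube, whereas "plasma from EDTA blood and serum are collected for proteomics, metabolomics and glycomics".

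**The concern.** The adequacy statement is a conclusion that the article itself draws, so it cannot be treated as detail left to a fuller document. It attaches to the wrong numbers, because enrolled counts are presented as retained ones. It also covers an analysis for which no sizing argument is given.

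A validated panel that predicts progression to severe dengue is a primary endpoint, and discrimination and calibration of the machine-learning models are a secondary endpoint. A reader who accepts the statement will expect stable models and reasonably precise performance from the discovery cohort. If the cohort supports only a handful of candidate parameters, complex models may look good in training, vary from fit to fit and lose performance in India, while the plan has already declared the size sufficient.

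**Working it through.** **1. The plan's own figure.** Inputs, all from the Statistical analysis section: 20,000 genes, 100 prognostic, power 0.8, FDR 0.01, control mean 5, dispersion 0.5, fold change 2, normalisation ratio 1. Sidedness is not stated; two-sided is assumed.

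- Per-gene alpha = 100 × 0.8 × 0.01 / (19,900 × 0.99) = 0.8 / 19,701 = 4.06 × 10⁻⁵.
- Exact negative-binomial test conditional on the total count: power 0.793 at n = 66 and 0.804 at n = 67. The smallest n is 67, as stated.
- Log-scale Wald check: variance term (1/5 + 0.5) + (1/10 + 0.5) = 1.3; n = (4.104 + 0.842)² × 1.3 / (ln 2)² = 66.2, which rounds up to 67.

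**2. Enrolled or retained.** 67 / 0.7 = 95.7, so 96, rounded up to 100. Hence 100 is the number before loss. After loss, 100 × 0.7 = 70 and 150 × 0.7 = 105. If 100 and 150 really were retained numbers, enrolment would have to be 100/0.7 = 143 and 150/0.7 = 215 per group, which contradicts Study status. The RNA-seq comparison is still safe: its power at 70 is 0.833.

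**3. What the calculation can say about a prediction model.** Its terms are mean count, dispersion, fold change, number of genes, power and FDR. None of them is the number of predictors, the expected model fit, the shrinkage or the precision of a performance measure.

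**4. Illustration of model size.** Assumptions that are not in the document: a binary model of severe dengue against the other two dengue groups, target shrinkage S = 0.9, Cox-Snell R² of 0.2 to 0.4. Retained discovery patients with dengue: 3 × 70 = 210, one third of them severe. The maximum number of candidate parameters is p = n × (S − 1) × ln(1 − R²/S).

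| R² | −0.1 × ln(1 − R²/0.9) | p at n = 210 |
|---|---|---|
| 0.2 | 0.0251 | 5.3 |
| 0.3 | 0.0405 | 8.5 |
| 0.4 | 0.0588 | 12.3 |

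The count is of candidates before any selection that uses the outcome. The omics features on offer are 20,000 + 1,034 + 1,200 = 22,234, before glycans and clinical variables.

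**5. Illustration of precision.** With an assumed true AUC of 0.80, Q1 = 0.80/1.20 = 0.6667 and Q2 = 2 × 0.64/1.80 = 0.7111. For 70 severe and 140 other patients, the Hanley-McNeil variance is (0.16 + 69 × 0.0267 + 139 × 0.0711) / 9,800 = 0.00121. The 95% half-width is 1.96 × 0.0348 = 0.068. With 100 and 200 patients it would be 0.057.

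**6. Patients with both RNA and plasma.** The document gives no loss rate for plasma. If d is an assumed plasma loss independent of RNA loss, pairs per discovery group = 100 × 0.7 × (1 − d): 70 at d = 0 or if losses fall wholly on the same patients, 63 at d = 10%, 49 at d = 30%.

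**The case against.** **No figure is miscalculated.** This stands: 67 and the step to 100 both reproduce. The error is the label retained and the conclusion drawn from it.

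**Machine learning is not rested on the RNA-seq result.** The adequacy sentence presents itself as going further than that calculation, and machine learning gets a separate rationale. That is a fair reading. But the rationale consists of safeguards. The planned Random Forest selection looks for association with severity, so it uses the outcome and does not reduce the candidate count in step 4. Dimension reduction that ignores the outcome would reduce it, but the document does not say to how many dimensions. External validation can reveal overfitting; it does not make the training set large enough.

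**The networks may never see 22,234 inputs.** Correct. Selection comes before training, and the figure describes the pool from which inputs are chosen.

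**Training may span both countries.** Leave-one-site-out validation allows this. With RNA and protein data pooled, 750 dengue patients leave 525 after 30% loss, and the same formula gives about 13 to 31 candidate parameters. That is more, but still small against 21,034 features, and the document does not state it as the basis.

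**Joint loss.** A reader might infer that the plan analyses complete cases only, and might multiply a separate 30% loss for every layer. The document supports neither. It gives no loss rate by layer and no complete-case rule, the AI section speaks of available data, and proteomics and metabolomics share plasma and serum specimens. Nor is 67 a threshold for integration, since it belongs to a gene-wise test. Differential analyses run layer by layer and need no joint profiles.

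**Conclusion.** The point holds in two parts. First, the adequacy sentence misstates its own numbers: about 70 and 105 per group are retained, not 100 and 150. This follows from the document alone. Second, adequacy for machine learning has no quantitative basis at either size. This also follows from the document, because no model-sizing quantity appears in it.

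The scale of about 5 to 12 candidate parameters at 210 patients rests on the assumed shrinkage, R² and binary outcome. The formula is for regression models and is only indicative for neural networks.

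A reader might take 5 to 12 as support for the planned panel of 5 to 10 proteins. It is not. The criterion counts candidates, and the panel is to be chosen from 1,034 proteins.

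The number with both RNA and plasma is at most about 70 per discovery group and lower if losses do not coincide; by how much cannot be told from the document. The RNA-seq sample size is unaffected.

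**What to change.** In the Statistical analysis section:

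- Describe 100 and 150 per group as enrolled, and give about 70 and 105 as retained after 30% loss.
- Strike machine learning from the adequacy sentence. Alternatively, replace the claim with the number of candidate parameters that the retained cohort supports, with the outcome contrast, expected R² and shrinkage stated, and counted before any outcome-driven selection.
- State that at most about 70 participants per discovery group will have both usable RNA and usable plasma, and fewer if losses do not coincide, with any assumed plasma loss shown as an assumption (for example 63 at 10%, 49 at 30%).

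In the section on AI models, label the multimodal neural networks exploratory.

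The cost is a few sentences and a less favourable adequacy statement. Recruitment targets need not change. With 170 of the 400 planned Guatemalan participants enrolled by June 2026, the correction can be made well before the models are trained on the full cohort.
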